#### Control group

Once patients were randomized, the control group continued to receive optimal medical care at the participating center. Exercise continued at a minimum frequency of three times weekly. The control patients received the same follow-up as the treatment arm, including an office visit in lieu of EBV implantation. At the time of the control arm office visit, all patients were provided with a study diary to be used as a memory aid throughout the study duration.

#### Treatment group

The study group received the EBV implantation procedure within three weeks of randomization, and continued optimal medical management and exercise similar to the control group.

The goal of the implantation procedure was to completely isolate a single diseased lobe of the lungs by implanting EBV devices occluding all bronchial lumina leading to the targeted lobe. Bilateral treatment was not allowed in this study and acceptable target lobes did not include the right middle lobe. A single segmental airway not isolated by valves may allow ventilation to the lobe, thus reducing the potential benefit of the EBV devices. EBV devices were placed at the lobar, segmental, or sub segmental levels in this order of preference, depending on the anatomy of the patient noted at the time of the procedure.

The EBV implantation procedure was performed with the patient under general anesthesia and on a ventilator, or under moderate sedation with unassisted breathing. All patients were given antibiotics before and for 7 days following the procedure. Anesthesia was administered according to standard local protocols for bronchoscopy. For general anesthetic procedures, a rigid bronchoscope in conjunction with a flexible bronchoscope or a flexible bronchoscope alone through an endotracheal tube was allowed for valve placement.

Patients in both control and treatment arms were monitored for 1 year, with scheduled assessments at 1, 2–3, 7–10, 30, 90, 180, and 365 days post-procedure. Follow-up assessment includes the same variables as in the baseline assessment (see Table 2) with the primary outcome measures defined from the 180 ± 14 day follow-up visit.

### Analysis

The power analysis is based on a pilot study in 38 patients in which FEV_1 _improved 14.9% ± 33.7 (mean ± SD) and 6 MWT distance improved 20.4% ± 41.5%. The samples size required to detect a 15% improvement in the treatment arm in FEV_1 _and a 17% improvement in 6 MWT distance at an alpha of 0.05 and a power of 0.90 is a minimum of 270 subjects with a 2:1 randomization to EBV procedure. Both of these values are above the threshold for minimal clinically important differences for these tests[17-19].

The study is designed as a superiority trial. For the two primary outcomes, the study is only considered a success if both endpoints show an improvement (one-sided test at p < 0.025). A one-sided test is appropriate to test for superiority. The actual probability of a false positive is lower than 0.025 given the imperfect correlation of the two endpoints. If change in FEV1 and change in 6 MWT were independent, the probability of a false positive would be 0.025*0.025 = 0.000625. In the pilot study generating the null hypothesis, the correlation coefficient between the change in FEV1 and 6 MWT was 0.3889. Given this r, the alpha for achieving a positive outcome is actually 0.005 (0.025*0.025^(1/(1+0.3889))). This is an assurance of avoiding a false positive well beyond convention.

The 2:1 randomization is chosen to enhance enrollment and increase the EBV population numbers in order to study covariates of treatment response. Although the 2:1 randomization increases the number of subjects required for the study, more robust subgroup comparisons may be possible.

For safety the 95% upper confidence interval for the Major Complication Composite rate delta between the EBV arm and the control arm is ≤ 30%.

The primary analysis cohort is intent to treat. As such, all 180 day missing data will be imputed using either a regression methodology if 30 and 90 day data are present or hot-deck imputation if there are not multiple datapoints available for a particular subject for regression analysis. Three unbiased imputations will be performed and the imputation resulting in the highest p-values will be selected as the final intent to treat dataset.

The initial analysis will evaluate the mean percent change between EBV and control in FEV_1 _and 6 MWT using an unpaired t-test if data are normally distributed or Mann-Whitney-Wilcoxon test if data require non-parametric testing. To determine if covariates impact the primary outcome variables, and to adjust for potential imbalances in randomization, both primary endpoints will be further tested via a multivariate model (SAS PROC MIXED). In order to reduce the possibility of over-specification of the model, the potential covariates listed in Tables 6, 7, 8, 9 will be subjected to a univariate screening procedure similar to that described by Hosmer and Lemeshow[20]. Derivations for these variables are provided in Table 10. Main effects and interactions with a p-value of 0.15 or less are allowed to enter a multivariate analysis using a mixed linear model (SAS PROC MIXED). The treatment effect must remain in the model in order to substantiate the one-tailed test of superiority. Those variables found to have statistically significant interactions with the treatment arm via the mixed model analysis will be further analyzed in follow-on sub-group analyses. In order to limit the impact of multiple hypothesis testing, univariate sub-set analysis will be performed using only those independent variables that remain in the mixed model as interactions with the treatment arm. For those analyses performed on the remaining independent variables, appropriate adjustments will be made to account for impact on Type I error[11]. Secondary endpoint analyses will follow the same methodology as described above.

**Table 6 T6:** Plethysmography, spirometry and HRCT derived baseline potential covariates*

Variable	Plethysmography/Spirometry	HRCT at TLC	HRCT at RV	TLC and RV HRCT ^†^
RV	X			
RV % Predicted	X			
TLC	X			
TLC % Predicted	X			
RV/TLC	X			
VC	X			
FVC	X			
FVC % Predicted	X			
FEV_1_	X			
FEV_1 _% Predicted	X			
FEV_1_/FVC	X			
Destruction Score of Target Lobe		X	X	
Ipsilateral Heterogeneity^††^		X	X	
Whole Lung Heterogeneity^††^		X	X	
For RUL Treatment Subset only: RUL-RML Heterogeneity^††^		X	X	
Target Lobe Volume % of TLC		X		
Target Lobe Volume % of RV			X	
Max Destruction Score other than target		X	X	
Min Destruction Score other than target		X	X	
Target Lobe Destruction Score % TLC-RV Delta				X
Target Lobe Volume % TLC-RV Delta				X
Fissure Score^†††^		X		

*Variables marked in multiple columns will be calculated twice, once using the expiratory (RV) CT and once using the inspiratory (TLC) CT. All tests are at Baseline.

^†^Some variables require information from both the TLC and RV CT

^†† ^Heterogeneity scores are derived by subtracting the minimum destruction score from the maximum destruction score.

^††† ^Fissure Score is an integer scale from one to three base on visual scoring by core center radiologists (1 = Fissure Absent, 2 = Incomplete Fissure, 3 = Complete Fissure).

**Table 7 T7:** Other baseline and procedure potential covariates

	Baseline	Procedure
Gender	X	
Age	X	
Site	X	
6 MWT	X	
Cycle Ergometry	X	
BMI	X	
DLCO % Predicted	X	
PaO_2_	X	
PaCO_2_		
Target Lobe		X
RUL Treatment		X
Upper vs. Lower		X
Right vs. Left		X
Valve Version*		X
Large Valve*		X
Small Valve*		X
Valve Combos*		X
Valve Expectorated*		X

*These potential covariates apply only to the treatment arm and do not have a control arm subset.

**Table 8 T8:** Composite or other potential covariate interactions

Composite or Interactions	Definition
Baseline BODE	BMI, FEV_1_% predicted, MMRC, 6 MWT Composite Score
NETT Strata	Randomization Stratification by Baseline Cycle Ergometry and HRCT at TLC
NETT Strata by Right vs. Left	Randomization Stratification by Baseline Cycle Ergometry and HRCT at TLC, by Right or Left Lung
Lobar Exclusion by Fissure Interaction*	Fissure Score = 3 AND Lobar Exclusion = Yes vs. all others
Lobar Exclusion, Fissure, and RV % Predicted*	Lobar Exclusion = Yes AND Fissure Score = 3 AND RV % Predicted ≥ 200% vs. all others
Lobar Exclusion, Fissure, and RV % Predicted*	Lobar Exclusion = Yes AND Fissure Score = 3 AND RV % Predicted ≥ 200% vs. all others
Large Valve by Right vs. Left*	Right vs. Left Lung AND Large Only vs. Others
Small Valve by Right vs. Left*	Right vs. Left Lung AND Small Only vs. Others
Expectorated Valve Replaced*	Valve(s) Expectorated AND Lobar Exclusion = Yes vs. all others
Expectorated Valve Not Replaced*	Valve(s) Expectorated AND Lobar Exclusion = No vs. all others
Lobar Exclusion by Site*	Technical Success by Site
First Case by Site*	First Treatment Case by Site vs. All Others
Learning Curve by Site*	Experience Level: Case 1, vs. 2 & 3, vs. 4–6, vs. 7–9, vs. ≥10 by site.

*These potential covariates apply only to the treatment arm and do not have a control arm subset.

**Table 9 T9:** 180 day follow-up CT potential covariate*

Variable	180 Day HRCT at TLC	Baseline and 180 Day HRCT at TLC	Baseline and 180 Day HRCT at RV
Target Lobe Atelectasis Score^†^		X	X
Lobar Exclusion^†† ^(yes/no)	X		

*These potential covariates apply only to the treatment arm and do not have a control arm subset.

^†^Atelectasis Score is a continuous variable from 0 to 100% and is defined as the % volume change in the target lobe from baseline to 180 day follow-up.

^††^Lobar Exclusion will be determined by the core lab radiologists and is defined as all airways into the target lobe are occluded by valves at day 180.

**Table 10 T10:** Covariate variable derivations

**Variable**	**Definition**
RV	Residual Volume by Spirometry and Plethysmography (TLC - Max (FVC or VC))
TLC	Total Lung Capacity by Plethysmography
VC	Vital Capacity by Plethysmography
FVC	Forced Vital Capacity by Spirometry
FEV_1_	Forced Expiratory Volume in the First Second by Spirometry
Target Lobe	RUL, RLL, LUL, or LLL
RUL	RUL Target vs. Others
Density Score	Density Score by Lobe
Total Density Score	Sum of all Lobar Density Scores (including RML)
Ipsilateral DS Heterogeneity	Target - Max DS of Non-treated Lobes within Treated Lung [e.g.: RUL - Max(RML, RLL)]
Thorax DS Heterogeneity	Target DS - Max DS of All Non-treated Lobes [e.g.: RUL - MAX (RML, RLL, LUL, LLL)]
Target Lobe DS % Delta	(TLC HRCT - RV HRCT)/TLC HRCT Density Score of Target Lobe
Target Lobe Volume % Delta	(TLC HRCT Volume - RV HRCT)/TLC HRCT Volume of Target Lobe
Fissure Score	Categorical Fissure Assessment Surrounding Target Lobe
	1 = Absent
	2 = Incomplete
	3 = Complete
NETT Strata	1 = Upper-Lobe Predominance, Low Baseline Exercise Capacity*
	2 = Upper-Lobe Predominance, High Baseline Exercise Capacity
	3 = Non-Upper-Lobe Predominance, Low Baseline Exercise Capacity
	4 = Non-Upper-Lobe Predominance, High Baseline Exercise Capacity
Target Lobe Atelectasis Scores	% change in Target Lobe Volume at TLC and at RV between Baseline and 180-day HRCT
Lobar Exclusion	Yes, If all bronchial pathways to target lobe are sealed by valve(s) – adjudicated by HRCT Core Lab
Valve Combinations	1. Small ONLY
	2. Small AND Large
	3. Large Only
Large Valve	Any procedure with Only Large Valves vs. all others
Small Valve	Any procedure with Only Small Valves vs. all others

*Low Exercise Capacity by Cycle Ergometry ≤ 25 W for Women, ≤ 40 W for Men

Thirty, 90, and 365 day results will also be collected and reported. Post hoc analysis will use these datapoints to define the speed of treatment success if present.

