## Methods

### Overview

VENT is a two-arm, randomized, controlled, multi-center trial designed to study the safety and efficacy of the EBV implantation procedure, and the ability of the EBV to produce sustained improvement of symptoms in emphysema. The study sample size was a minimum of 270 subjects with heterogeneous emphysema, with randomization at a ratio of 2 to 1 (*i.e., *two patients were randomized to the study device treatment arm for every one randomized to the control group).

Given the similarity in intended treatment effect between LVRS and EBV implantation, combined with a goal of allowing easy comparisons between the results of the NETT and VENT, the VENT design largely followed that of the NETT. The inclusion/exclusion criteria were similar and both studies required pulmonary rehabilitation prior to randomization in order to maximize function prior to intervention. Both studies allowed treatment of the upper or lower lobes based on CT analysis; however, the NETT required bilateral (left and right lung) treatment whereas VENT treatments were unilateral only. Patient randomization in VENT was stratified per the subgroups identified in the NETT according to lung treatment region (upper versus lower) and post rehabilitation pre-treatment exercise capacity (low versus high).

In addition, the VENT study design conformed to the consensus recommendations of an independent panel of physician specialists convened by the U.S. Food and Drug Administration in February of 2003 to provide study design input for emerging bronchoscopic treatments for emphysema[10]. Questions considered at the panel included appropriate control groups, safety assessment, appropriate outcome metrics, and length of follow up.

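### The 0.90 power for 270 subjects fits one-sided 0.05 per endpoint; under the stated success rule (both endpoints at one-sided 0.025) it is about 0.84

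*Protocol article*

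**What the plan says.** Everything needed is in the Analysis section of the protocol article, apart from the allocation, which the Overview also gives ("with randomization at a ratio of 2 to 1").

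- Pilot data from 38 patients: FEV1 "improved 14.9% ± 33.7 (mean ± SD"), and "6 MWT distance improved 20.4% ± 41.5"%.
- Design effects: the trial is sized to "detect a 15% improvement in the treatment arm in FEV_1 _and a 17% improvement in 6 MWT distance".
- Sample size: the number required for this "at an alpha of 0.05 and a power of 0.90 is a minimum of 270 subjects with a 2:1 randomization to EBV procedure". The sentence does not say whether the alpha is one-sided or two-sided, or whether the power is per endpoint or for both.
- Success rule, one paragraph later: "the study is only considered a success if both endpoints show an improvement (one-sided test at p < 0.025").
- Correlation: the pilot value of 0.3889 is given, but it is used only to argue that a false positive is unlikely. Power under the success rule is not stated.

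**The concern.** Requiring both endpoints lowers the false-positive rate, as the article says, but it also lowers power, and the article does not show that cost. A reader will take 0.90 as the chance that the trial succeeds if the device works as assumed. If 0.90 was obtained at a more lenient alpha than the one in the success rule, that chance is overstated. The figure matters most if the trial misses on one endpoint, because the stated power then shapes how the miss is read.

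**Working it through.** **Inputs from the article.** Effects 15% and 17%; SDs 33.7 and 41.5; 270 patients at 2:1, so 180 and 90; correlation r = 0.3889; both endpoints required, each at one-sided 0.025.

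**Assumptions not in the article.** The pilot SD applies in both arms, and the mean change in controls is zero. Normal approximation throughout.

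**Standardised effects.** SE = SD × √(1/180 + 1/90) = SD × 0.1291.
- FEV1: SE = 33.7 × 0.1291 = 4.351; 15 / 4.351 = 3.448.
- 6MWT: SE = 41.5 × 0.1291 = 5.358; 17 / 5.358 = 3.173.

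**Step 1: reproduce the article's figure.** Take alpha 0.05 as one-sided (critical value 1.645) and require both endpoints.
- FEV1: Φ(3.448 − 1.645) = Φ(1.803) = 0.964.
- 6MWT: Φ(3.173 − 1.645) = Φ(1.528) = 0.937.
- Both, r = 0: 0.9643 × 0.9368 = 0.903. The next smaller 2:1 total, 267, gives just under 0.90 (0.8997), so 270 is exactly the required number.
- Both, r = 0.3889 (bivariate normal): 0.909; here 264 would suffice.

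The other readings do not give 270. Each endpoint alone at one-sided 0.05 needs 195 (FEV1) and 231 (6MWT). Each alone at two-sided 0.05 needs 240 and 282.

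**Step 2: apply the stated success rule.** Critical value 1.960.
- FEV1: Φ(3.448 − 1.960) = Φ(1.488) = 0.932.
- 6MWT: Φ(3.173 − 1.960) = Φ(1.213) = 0.887.
- Both:

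| Correlation | Joint power |
|---|---|
| 0 | 0.827 |
| 0.3889 (stated) | 0.840 |
| 0.6 | 0.851 |
| 0.8 | 0.866 |
| upper limit, any r | 0.887 |

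The limit holds because success on both cannot be likelier than success on the weaker endpoint. A simulation of 40,000 trials with pooled t-tests at r = 0.3889 gave 0.839 for both, 0.930 for FEV1 and 0.888 for 6MWT.

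**Step 3: vary the unstated control SD.** With SE = SD × √(1/180 + f²/90), where f is the ratio of control SD to pilot SD, at r = 0.3889 and one-sided 0.025:

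| f | Joint power |
|---|---|
| 0.85 | 0.916 |
| 0.88 | 0.903 |
| 0.90 | 0.893 |
| 0.95 | 0.868 |
| 1.00 | 0.840 |
| 1.10 | 0.779 |

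**Step 4: effects that give joint 0.90 at N = 270.** With f = 1 and r = 0.3889, effects of 16.2% and 18.4% give Φ(1.764) = 0.961 and Φ(1.474) = 0.930 separately, and 0.901 jointly.

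**The case against.** The strongest reply is that the sample-size sentence is not a miscalculation. It says alpha 0.05, the trial's tests are one-sided, and on that reading 270 gives 0.90 even jointly. This stands. A reader might infer that the sponsor got the arithmetic wrong, but the article does not support that: the sizing alpha and the testing alpha differ. Nor does the article say how 270 was reached, so the exact match at one-sided 0.05 with r = 0 is a likely explanation, not a documented one.

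The second reply is that 0.84 rests on a control SD and a control change that the article does not give. This also stands. The smaller arm supplies two-thirds of the variance, since 1/90 is twice 1/180. A control SD about 12% below the pilot value would restore joint 0.90; one 10% above it would take power to 0.78. The article gives no reason to prefer either direction.

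The pilot means in place of the design effects (14.9% and 20.4%) would give 0.905 for both at one-sided 0.025. But the article says that the design is for 15% and 17%.

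Two further inferences are tempting and should not be drawn. One is that 6MWT alone is underpowered: 0.887 against 0.90 is ordinary rounding, and a control SD 5% lower gives 0.907. The other is that missing data were ignored. A condensed article commonly leaves the dropout allowance to the full protocol, it calls 270 a minimum, it plans imputation, and it gives no missing-data rate from which to calculate a loss.

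**Conclusion.** The point holds as an inconsistency between the sizing statement and the success rule. Under the stated rule, joint power at 180 versus 90 is about 0.84, so a device that works exactly as assumed would fail the rule in about 16% of trials (1 − 0.84), against the 10% that the text implies. This rests on the pilot SDs in both arms, zero control change and r = 0.3889. With those SDs, no correlation brings the figure to 0.90. Across control SDs of 0.85 to 1.1 times the pilot value, joint power runs from 0.92 to 0.78, so 0.84 is a central value under stated assumptions, not an exact one.

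A reader might conclude that the trial is too small or that its result is unsafe. Neither follows. The false-positive rate is untouched, the test and the decision rule do not depend on the power figure, and the stated number of patients can stand if its power is described correctly.

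**What to change.** Keep N at 270 and change the wording of the Analysis section:

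1. Give alpha as one-sided 0.025 per endpoint in the sample-size sentence as well as in the success rule.
2. State the assumed SD and mean change in the control arm.
3. Restate power, for example: with 180 and 90 patients, effects of 15% and 17%, pilot SDs in both arms, no control change and correlation 0.39, power is 0.93 for FEV1, 0.89 for 6MWT and about 0.84 for success on both.

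As an alternative to step 3, keep 0.90 and say that, on the same assumptions, it is the joint power for effects of about 16.2% and 18.4%. If the sponsor has a different control SD, the figures should be recalculated with it.

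The cost is a few sentences and a less favourable stated power. No patients, tests or decision rules change.

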Advanced emphysema is characterized by destruction of lung parenchyma and augmentation of anatomic connections for air passage between adjacent lung lobules. Unfortunately for endobronchial lung volume reduction procedures, these collateral communications may traverse lobar fissures [25]. These peripheral communications between lobes then may allow for continued lobar ventilation despite completely occluded lobar airways. Because this collateral ventilation is not easily quantified by current detection methods, the outcome of EBV valve placement may be heterogeneous. Ultimately, secondary analyses will include responder analysis, in order to determine the proportion of patients with clinically meaningful responses.

Given the complex mechanical and gas exchange consequences of valve insertion, it is possible that the magnitude of volume reduction in a lobe may not be associated with changes in other meaningful physiologic or functional indices following the procedure. For example, the impact of valve placement on symptoms associated with dynamic hyperinflation or variations in gas exchange utilizing collateral channels may be associated with clinical improvements independent of changes in conventional resting pulmonary tests. The composite primary endpoint was chosen to include a functional exercise measure to capture such changes.

Ultimately, the future of the EBV valve will be determined by the balance between efficacy and safety. Since the valves are removable for mild or moderate adverse events, valve safety will be impacted by the frequency of severe adverse events that might affect survival in a compromised patient population. In fact, individuals who demonstrate improvements in lung function may also demonstrate an increase in exacerbation frequency. For this reason, quality of life indices including the Quality of Well Being Scale and the Saint George's Respiratory Questionnaire are considered integrative parameters which can determine the balanced impact of the intervention [26,27]. One strategy to minimize overall adverse response would be to remove valves earlier in the patients who do not have clinically important responses. If a meaningful outcome is measurable in the first few days after the procedure, future alternative targeting strategies might be employed to determine response at earlier times after randomization.

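### The stated overall alpha of 0.005 covers only the case where neither endpoint has an effect; the co-primary rule controls the false-positive rate at a maximum of 0.025

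*Protocol article*

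**What the plan says.** The Analysis section sets the success rule: "the study is only considered a success if both endpoints show an improvement (one-sided test at p < 0.025"). It then argues that the true error rate is smaller than the nominal one: "The actual probability of a false positive is lower than 0.025 given the imperfect correlation of the two endpoints". Two figures follow. Under independence, "the probability of a false positive would be 0.025*0.025 = 0.000625". For the correlated case it reports that in the pilot "the correlation coefficient between the change in FEV1 and 6 MWT was 0.3889", and continues: "Given this r, the alpha for achieving a positive outcome is actually 0.005 (0.025*0.025^(1/(1+0.3889"))). The paragraph concludes: "This is an assurance of avoiding a false positive well beyond convention".

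**The concern.** Multiplying two tail probabilities, or adjusting that product for correlation, gives the chance that both tests pass when neither endpoint has an effect. The trial's claim is that both improve, so its null hypothesis is that at least one does not. That null includes every case in which one endpoint improves and the other is flat. The quoted alpha leaves those cases out, and they are where the error is largest.

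Such cases are not remote here. The Discussion says that "the magnitude of volume reduction in a lobe may not be associated with changes in other meaningful physiologic or functional indices", adds that clinical gains may arise independently of resting lung function tests, and gives this as the reason for including an exercise endpoint. Study limitations adds that, without blinding, a placebo effect could influence the exercise measurements. A reader who accepts 0.005 would credit a positive result with about five times more protection than the rule guarantees. The printed formula also does not evaluate to the printed figure.

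**Working it through.** **Inputs, all from the Analysis section:** one-sided 0.025 per endpoint (critical value 1.96); both must pass; r = 0.3889; 270 subjects at 2:1, taken as 180 versus 90; pilot SDs 33.7 (FEV1) and 41.5 (walk distance); design effects 15% and 17%; pilot of 38 patients.

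**Assumptions not in the document:** the two test statistics are bivariate normal with correlation equal to the pilot r; the pilot SDs hold in both arms; r comes from the same 38 patients as the power inputs.

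**Step 1. Reproduce the 0.005.**
- As printed: 0.025 × 0.025^(1/1.3889) = 0.025 × 0.025^0.720 = 0.00176. This is not 0.005.
- With the product in brackets: (0.025 × 0.025)^(1/1.3889) = 0.000625^0.720 = 0.00493. This rounds to 0.005.

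The bracketed form gives 0.000625 at r = 0 and 0.025 at r = 1, both correct. The stated figure most likely comes from that form, with a bracket pair lost in print.

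**Step 2. The both-null probability.**
P(Z1 > 1.96 and Z2 > 1.96; r = 0.3889) = 0.0032. The bracketed formula (0.0049) is an ad hoc interpolation that exceeds this value.

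The pilot r is imprecise. On the Fisher scale, atanh(0.3889) = 0.4105 with standard error 1/√35 = 0.169. The approximate 95% interval for r is 0.08 to 0.63, and the both-null probability then runs from 0.0009 to 0.0068.

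**Step 3. One endpoint null, the other with noncentrality θ.**
The false-success probability is P(Z1 > 1.96 and Z2 > 1.96 − θ; r = 0.3889).

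| θ of the improving endpoint | P(false success) |
|---|---|
| 0 | 0.0032 |
| 1 | 0.0119 |
| 2 | 0.0212 |
| 3 | 0.0245 |
| 4 | 0.0250 |

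**Step 4. θ at the design effects.**
√(1/180 + 1/90) = 0.1291.
- FEV1: θ = 15 / (33.7 × 0.1291) = 15 / 4.351 = 3.45. If only FEV1 improves, P(false success) = 0.0249.
- Walk distance: θ = 17 / (41.5 × 0.1291) = 17 / 5.358 = 3.17. If only walk distance improves, P(false success) = 0.0247.

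**Step 5. The bound.**
P(both pass) cannot exceed P(the null endpoint passes) = 0.025, and it approaches 0.025 as θ grows, whatever the correlation. At moderate θ the correlation does matter: at θ = 1 the probability is 0.0055 for r = 0.08 and 0.0184 for r = 0.63. At the design effects it matters little. Even with independent statistics the result is 0.025 × power, which is 0.025 × 0.932 = 0.0233 (only FEV1 improves) or 0.025 × 0.887 = 0.0222 (only walk distance improves).

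**Ratio to the stated figure:** 0.025 / 0.005 = 5.

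**The case against.** The strongest reply is that nothing depends on the 0.005. The success rule controls the error at 0.025 under every configuration, no threshold was relaxed, and the sample size is stated at its own alpha and power. That stands, and it is why no design change is asked for. It does not rescue the figure, which is presented as the alpha of the primary claim and used to support an explicit assurance.

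The following also stands:

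- A reader might infer that the formula is absurd because, as printed, it gives 0.004 at r = 1 where the answer must be 0.025. The document does not support that inference: it writes the product 0.025 × 0.025 as the joint probability just before, and the bracketed form passes the r = 1 check. Measuring the error against 0.0018 would exaggerate it for the same reason.
- A reader might infer that the trial's actual false-positive rate is 0.025. That is too strong. The rate depends on unknown true effects and runs from about 0.003 with both null to just under 0.025. The sentence saying the probability is lower than 0.025 is literally true for any finite effect; what fails is the reason it gives, imperfect correlation, and the size it goes on to attach.
- The both-null value of about 0.003 is not exact. It needs bivariate normality, the plan allows a rank test instead of the t-test, and 0.005 lies inside the range produced by the uncertainty in r. For the both-null case alone, the document's figure errs on the cautious side.
- The quoted Discussion sentence concerns lobar volume reduction against other indices, not FEV1 against walk distance. It shows that divergence was contemplated, but does not show how likely it is.

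**Conclusion.** Wrong as written, and correctable by wording. The 0.005 applies only when neither endpoint has an effect. Over the full null, where at least one endpoint does not improve, the false-positive probability has a maximum of 0.025. It comes within 0.0003 of that bound when one endpoint has its design effect and the other has none. The claim of protection beyond convention is unsupported: the rule gives the conventional level.

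The 0.025 bound needs only that each test holds its own level. The intermediate values rest on bivariate normality and the pilot r; the design-effect values also rest on 180 versus 90 subjects and pilot SDs in both arms. The mismatch between the printed expression (0.0018) and its stated result is secondary and most likely a lost bracket pair. Nothing here suggests that the success rule is invalid or the sample size wrong on this account.

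**What to change.** Keep the decision rule. Delete the independence figure, the 0.005, its formula and the closing assurance, and replace the sentence that credits imperfect correlation for a rate below 0.025. Suggested text: *Requiring both endpoints at one-sided 0.025 controls the false-positive rate at no more than 0.025; this bound is approached when only one endpoint truly improves.*

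If a both-null figure is kept, give about 0.003, label it as applying only when neither endpoint has an effect, and state its assumptions (bivariate-normal statistics, pilot r) with the range of roughly 0.001 to 0.007.

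The cost is a few sentences. The success rule and the sample size do not change; the only loss is a claim of extra protection that the design does not provide.
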